### Oversight, monitoring and dissemination

#### Data monitoring

As the intervention has a short duration and minimal known risks, there is no need for a formal data monitoring committee or interim analyses. The principal investigator and project coordinator keep close contact with all participating units and any issues regarding recruitment, intervention, and project overall will be managed continuously. The principal investigator and project coordinator also continuously monitor the project progress and project data (i.e., its completeness and accuracy), and if necessary, consult others in the data management group.

#### Harms

No harms are expected through participation. However, LEAP participants sacrifice time and energy to take part in a treatment program with uncertain benefits while individuals randomized to control group may be disappointed that they will not receive LEAP. Further, although self-rating symptoms as all participants do through BASS is unlikely to be harmful, it may raise concern. Therefore, in all stages of data collection (in visible materials, in BASS, etc.), contact details to the PI are provided, encouraging participants to contact her in case of questions or concerns. Both PI and PC are clinical psychologists and clinicians and/or participants can contact any of them for guidance if needed. As LEAP is delivered in groups, sensitive information might be shared, why the therapists need to make sure that in the first session of every new LEAP group that all participants agree upon a code of conduct. All LEAP therapists are experienced clinicians at the units where participants have an active treatment. Thus, if adverse events arise, participants have access to care and can be monitored. LEAP therapists are also instructed to register any issues related to the LEAP intervention groups, including potential adverse events. This is reported to the PI and managed with appropriate actions.

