#### Study consent

Subjects are first informed orally by project affiliated unit staff with extensive knowledge on the project, followed by oral or written information from the project manager (also the LEAP principal investigator; PI) or project coordinator (PC). Formal participant information and written study consent are managed and collected through the online data collection and participant management system BASS Core Facility (BASS; see *Data collection and management*) using a governmentally and financially approved secure electronic signature system (Bank-ID; https://www.bankid.com/en). Written participant information in BASS include details about the project, participation, potential risks and benefits of participation, usage of participant data, how to find study results, insurance and remuneration, and the voluntary basis of participation. Contact details to the PI, the KI Data Protection Officer and the Swedish Data Protection Authority are also provided. Patients consent to project participation, to medical records being collected and to have their data collected as described. There are no ancillary studies; all collected data are related to this project.

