##### Modifications and discontinuation

LEAP will not be modified for individual participants. There are no formal criteria for intervention discontinuation; LEAP-therapists discuss potential adverse events for individual participants (e.g., severe psychiatric deterioration) with the PI who then formally decides on possible intervention discontinuation. No additional assessments are required in case of treatment discontinuation or study withdrawal.

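### The only adverse-event registration described is by LEAP therapists for the LEAP groups, so discrete adverse events cannot be compared between arms

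*Protocol article*

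**What the plan says.** The protocol article deals with adverse events in two places.

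- **Harms:** "LEAP therapists are also instructed to register any issues related to the LEAP intervention groups, including potential adverse events". The next step is case handling: "This is reported to the PI and managed with appropriate actions".
- **Modifications and discontinuation:** "LEAP-therapists discuss potential adverse events for individual participants (e.g., severe psychiatric deterioration) with the PI", who then decides whether the intervention stops for that person.

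The Harms section also describes contact routes open to both arms. For participants, "contact details to the PI are provided, encouraging participants to contact her in case of questions or concerns"; and because the PI and project coordinator are clinical psychologists, "clinicians and/or participants can contact any of them for guidance if needed". Neither sentence says that such contacts are logged as events.

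The expectation is stated as "No harms are expected through participation". Under Data monitoring the short duration and minimal known risks lead to the position that "there is no need for a formal data monitoring committee or interim analyses". The Statistical methods section describes no comparison of adverse events.

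**The concern.** Both recording routes have the same reporter and concern the same arm. The protocol's own example of an event, severe psychiatric deterioration, can also occur under treatment as usual alone. If such an event happens in a control, nobody is instructed to record it.

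Within the LEAP arm the register is also partial. It is tied to the groups, so it can miss events while a patient waits for a group to fill, events after the programme ends, and events in patients who were allocated to LEAP but never attended.

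What is at stake is the reporting of harms. The Discussion names national implementation as the goal if LEAP proves beneficial. A statement at that stage about discrete adverse events would rest on data from one arm, with no randomised comparator.

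**Working it through.** The protocol states no harms figure, so there is none to reproduce. The check has three parts.

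**1. What is collected in which arm**

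| Information | LEAP + TAU | TAU | Where stated |
|---|---|---|---|
| Adverse events registered by a named reporter | Yes, LEAP therapists | None described | Harms; Modifications and discontinuation |
| Spontaneous contact with PI or coordinator | Open | Open | Harms |
| EDE-Q, CET, DERS, DSM-5 symptoms at T2 and T3 | Yes | Yes | Table 2; Self-report and interview data |
| SEDI and BMI at T3 | Yes | Yes | Instruments/measures |
| Dropout and loss to follow-up | Yes | Yes | Statistical methods |

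Only the first row differs by arm, and it is the only row that records discrete events. Admission and self-harm are not listed as outcomes. Under Concomitant care, LEAP therapists are encouraged not to treat trial participants individually. They are therefore poorly placed to see events in controls, and the instruction to register covers the LEAP groups in any case.

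**2. How much of follow-up the register spans**

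Inputs: group sessions over four consecutive weeks, or 28 days (LEAP section); participation of at least 182 days (Participant timeline).

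28 / 182 = 0.154

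The group phase covers about 15% of the minimum follow-up. The individual session and informal contact may widen this somewhat, but nothing in the text extends registration to T3.

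**3. What equal collection could show**

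Input: 64 per arm (Sample size). The event rates are assumptions, because the protocol gives none.

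Half-width of the 95% interval for a risk difference with equal rates p: 1.96 × √(2p(1 − p)/n).

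- n = 64, p = 5%: 1.96 × √(2 × 0.05 × 0.95 / 64) = 7.6 points
- n = 64, p = 10%: 1.96 × √(2 × 0.10 × 0.90 / 64) = 10.4 points

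With the expected 30% dropout, questionnaire items alone would reach 64 × 0.70 = 44.8, about 45 per arm. The half-widths then become 9.0 and 12.4 points.

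Power, two-sided 5%, normal approximation: Φ[(|p₂ − p₁| − 1.96·SE₀)/SE₁], with SE₀ from the pooled rate and SE₁ from the separate rates.

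| Assumed rates | 64 per arm | 45 per arm |
|---|---|---|
| 5% vs 15% | 47% | 35% |
| 5% vs 20% | 73% | 58% |
| 10% vs 20% | 35% | 26% |
| 10% vs 30% | 82% | 67% |

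Equal collection removes the ascertainment bias tied to who does the recording. It does not give a sensitive test for uncommon harms.

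**The case against.** The strongest reply is that worsening is already measured in both arms. The symptom scales are completed by everyone at T2 and T3, descriptive results are promised for all 13 general-psychopathology domains, the clinicians doing the diagnostic assessments are blinded, and dropout is tested between groups. Severe deterioration is therefore partly captured without regard to arm. This stands, and it limits the point to discrete events. It does not close the gap, for two reasons. Modifications and discontinuation requires no further assessment after withdrawal, and Statistical methods sets aside a time point that lacks CET or EDE-Q. A patient who deteriorates and stops responding may leave no data, although the protocol does not show that such patients are the ones who are lost.

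A second reply is that no table of events by arm is planned, no safety objective is stated, and a condensed article may leave event definitions and forms to the full protocol. The first two parts are true. The third does not answer the point: the article does not merely omit a detail, it assigns registration to one arm. The discontinuation passage is weaker evidence, since stopping LEAP can only concern LEAP participants.

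Two stronger readings are tempting, and the documents support neither:

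- A reader might infer that the trial can say nothing about the safety of adding LEAP. That goes too far, because the outcomes measured in both arms remain comparable.
- A reader might also infer that one-sided registration would produce a statistically significant false excess under LEAP. That requires near-complete capture. With an assumed 10% rate, 6.4 events are expected among 64 patients. If they were spread evenly over 182 days and caught only in the group phase, 6.4 × 28/182 ≈ 1 would be registered. The event rate and the capture are both unknown, so no figure for a false excess is justified.

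**Conclusion.** The point holds in a limited form. As written, adverse events are actively registered only in connection with the LEAP groups, and their counts cannot support a comparison between arms. Mean symptom change, BMI at T3, diagnosis at T3 and dropout are unaffected, and so is the efficacy analysis.

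The conclusion rests on the text describing no other register. The open contact routes to the PI and coordinator could in practice be logged, but nothing says that they are. The direction of bias in a raw count by arm would be against LEAP; its size cannot be stated from the documents. The change is worth making, because it is cheap and the Trial status section says that recruitment has not begun.

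**What to change.** Ascertain events with the same definitions, in the same way and over the same T1 to T3 window in both arms.

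1. At T3, extract admissions and serious events from the medical record for every randomised participant who has not withdrawn consent to record access. Participants agree "to medical records being collected and to have their data collected as described", and Data management already describes a transfer route for record data. This source also covers patients who miss T2 or T3. The extracted fields should not mention LEAP attendance, because the Blinding section keeps allocation from the PI until the main effects have been analysed.
2. Add two or three fixed items to the T2 and T3 BASS battery for everyone, covering deterioration, admission or a higher level of care, and self-harm since the last assessment. In an open-label trial the answers may still be coloured by knowledge of allocation, which is a further reason to have the record data.
3. Compare the arms in the randomised set by a risk difference with a 95% confidence interval, and state that 64 per arm can detect only large differences.
4. Keep therapist registration for case handling, and report it separately as LEAP-only, non-comparative data.

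If none of this is adopted, any safety statement should be confined to the outcomes measured in both arms.

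The cost is about a minute of participant time, some record extraction at four units, and an ethics amendment, for which Protocol amendments already provides.

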#### Auditing

No formal auditing is included in the project.

#### Protocol amendments

Modifications in the protocol are communicated to participating units (i.e., LEAP-therapists, research staff; managers, other staff when necessary). Minor modifications may be communicated via e-mail to those concerned, other modifications are communicated through meetings. For significant modifications related to the participants (e.g., eligible criteria, recruitment, assessment, intervention, etc.) or other significant changes, amendments to the ethical permit are applied for. Major modifications (e.g., delays due to covid-19) are also reported to financers and updated in the ISRCT registry.

#### Dissemination policy

Trial results will be published in peer-reviewed psychiatric journals, preferably Open Access to enable wider dissemination. Results will be presented for staff at participating units, to other health-care professionals (e.g., through interest organizations, at research conferences). Results may also be promoted by a public press release and posts on social media. The PI (EFM) is main or senior author, the PC (EM) is co-author on all manuscripts from the project, and the LEAP originator CM is expert advisor. Other authors are based on manuscript contribution. The intervention manual will be available upon demand from the LEAP originator and the PI. Data will not be shared outside of the project group, but meta data will be available upon demand if ethical permits exist (e.g., for meta-analyses).

#### Trial status

Everything is prepared for the study to commence. Collaboration with units is well established, procedures for data collection and recruitment procedures are finalized, and the LEAP training for therapists are completed. However, due to Covid-19 restrictions prohibiting non- essential group interventions at the clinics, recruitment has not been able to start yet. As Covid-19 vaccinations are currently initiated and restrictions possibly eased later on as a result, we plan to start recruiting during the late spring of 2021 with LEAP intervention groups starting as close to recruitment as possible.

## Discussion

The overall project aim is to evaluate the efficacy of the LEAP program targeting CE, modified to suit a population of mixed EDs with CE within an outpatient specialized ED treatment setting. To our knowledge, this is the first study to include patients with other ED diagnoses than AN, when evaluating LEAP. Since CE is a prominent symptom in various ED presentations and is linked to a more negative prognosis, CE requires attention in ED treatment when the patient presents with this problem behavior. LEAP is one of few attempts to address CE systematically and it has the advantage of being a stand-alone, brief treatment delivered as an add-on to standard ED care, thus suitable for almost all patients with CE as a symptom. The present study is naturalistic, which means LEAP will be studied in the setting and form it is intended to work, as opposed to a more controlled scientific context. This is also unique and will provide valuable new information about implementing LEAP in standard ED care.

Currently, about 50% of patients report at least some CE and may therefore benefit from this treatment in terms of overall improved general and ED specific pathology and quicker ED remission. LEAP provide patients with increased knowledge and understanding of the mechanisms that maintain a compulsive stance towards exercise; LEAP also provides tools for promoting healthy and balanced exercise, which is important for relapse prevention. Prior studies have shown that LEAP has positive effects on CE and ED pathology, LEAP also reduced time in inpatient care for individuals with AN. In summary, LEAP has the potential of improving remission, which is of significant importance to afflicted, their families, and the society as a whole in terms of reduced healthcare costs. If LEAP shows beneficial effects in this trial, the goal is to implement LEAP nationally in Sweden. The project group has well-established contacts with the majority of Swedish ED units and as such, is well suited to inform and educate clinicians in the LEAP method. Hopefully, LEAP meets a demand which so far has not been met in specialized ED care. The results of the study will also be disseminated internationally via peer-reviewed journal articles and scientific conferences.

The major trial concerns are related to inclusion pace and LEAP group initiation. As LEAP requires at a minimum 4 participants and because of the randomization procedure, units need to recruit more than twice as many patients at a time to ensure that LEAP groups can start as soon as possible. Recruitment may also be complicated by the RCT-design: potential participants experiencing difficulties related to CE and wanting the intervention may be discouraged from study participation as they may be randomized to the control group. LEAP initiation is not only complicated by participant influx; Covid-19 restrictions has prohibited non-essential group interventions at the clinics and therefore delayed the project. As of now, the hope is that timely vaccination will enable group interventions prior to the summer 2021; in that case, recruitment can start immediately.

### Research ethics approval

The study was approved by the Swedish Ethical Review Agency (number: 2020–01173).

## Data Availability

Not applicable.

## Abbreviations

AN: Anorexia Nervosa
AI: Allocating Investigator
Bank-ID: Bank identification (personal electronic authorization method)
BMI: Body Mass Index
BN: Bulimia Nervosa
CBT-E: Cognitive Behavioral Therapy-Enhanced
CE: Compulsive Exercise
CET: Compulsive Exercise Test
CM: [name]
DBA: Data Base Administrator
DERS: Difficulties in Emotion Regulation Scale
DSM-IV: Diagnostic and Statistical Manual of Mental Disorders, version 4
DSM-5: Diagnostic and Statistical Manual of Mental Disorders, version 5
ED: Eating Disorder
EDE: Eating Disorder Examination
EDE-Q: Eating Disorder Examination Questionnaire
EFM: [name]
EM: [name]
KI: Karolinska Institute
LEAP: The CompuLsive Exercise Activity TheraPy
OSFED: Other Specified Feeding and Eating Disorders
Patient ID: Patient identification
PC: Project coordinator
PI: Principal Investigator
RCT: Randomized Controlled Trial
SEDI: The Structured Eating Disorder Interview
TAU: Treatment As Usual
TC: [name]
T1: Timepoint 1 (baseline)
T2: Timepoint 2 (3 months follow-up)
T3: Timepoint 3 (6 months follow-up)
